| **Cardiovascular** involvement for inclusion and allocation to primary or secondary organ failure by critical care specialists:   - Hypotension without *severe* respiratory symptoms - Dizziness or feeling faint without *severe* respiratory symptoms - Dyspnoea without severe respiratory symptoms/increase work of breathing. - Postural dizziness without severe respiratory symptoms - Sweating and nausea without severe respiratory symptoms - Tachycardia meeting red ViCTOR^4^ criteria prior to adrenaline and without severe respiratory symptoms - Requiring ongoing vasopressor support even if respiratory symptoms present - Negative/not for inclusion if cardiac arrest only manifestation recorded. |

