| **Purpose and basis for reporting guide** | All patients in this study are deceased and have the most severe grade of anaphylaxis. However deterioration occurs after experiencing less severe grades of anaphylaxis (within varied time frames).  Severe symptoms in this study represent a clinical state occurring prior to arrest. It is an opportunity to examine treatment and situational factors before the patient ultimately enters the peri-cardiorespiratory arrest state. They represent symptoms and signs where there is objective evidence of severe disease and the patient is aware that they need urgent help.  Reporting guidance is based on Grade 3 features developed by Brown^3^ and symptoms statistically significant for hypotension or hypoxia documented in the same analysis. The latter are included to allow for lay reports (eg police reports) to be analysed systematically. Grade 3 Australian New Zealand College Anaesthethetists^21, 28^ and Rapid Review Team/MET criteria represented in the Victorian Childrens Tool for Observation and Response (VICTOR) are also incorporated (eg clinical review triggers)^4^.  Exact times recorded where available. Estimated times recorded where possible to nearest minute for 1-4 minutes, nearest likely 5 minutes for 5-30minutes, nearest 10 minutes greater than 30 minutes. | | |
| **Outcome #** | **Outcome Text Label** | **Outcome Text Label** | **Definition Note** |
| N/A |  |  |  |
|  |  |  |  |

- 1. **Arrest – time to**

| **Definition** | Cardiorespiratory arrest prior to death, or prior to hypoxic brain injury leading to death. | | |
| --- | --- | --- | --- |
| **Field Size** |  | **Date started** | 01/05/2024 |
| **Reporting guide** | Cardiorespiratory arrest = Arrest  Arrest occurs when there is   - Sudden bradycardia - Loss of pulse or BP <50 - Unconscious with ineffective breathing needing assisted ventilation - Seizure or myoclonic activity (hypoxic/hypotensive) - Shockable rhythm/asystole   Exact times recorded where available. Estimated times recorded where possible to nearest minute for 1-4 minutes, nearest likely 5 minutes for 5-30minutes, nearest 10 minutes greater than 30 minutes. | | |

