**ORGAN FAILIRE TYPES**

- 1. **Upper Airway Oedema present**

| **Definition** | Upper Airway Oedema present during the anaphylaxis episode | | |
| --- | --- | --- | --- |
| **Data name** | Airway Oedema | **Collection** | Manual extraction |
| **Data Type** | Single answer | **Date Started** | 01/05/2024 |
| **Field Size** | Drop down yes/no/not recorded | **Layout** |  |
| **Code Set** | [airway_oedema] = '1' |  |  |
| **Reporting guide** | Yes if ANY of the following present   - Stridor - Altered voice - Tongue/oropharyngeal swelling - Obvious laryngeal swelling at 1^st^ laryngoscopy - Gross macroscopic laryngeal swelling at autopsy | | |
| **Purpose and basis for reporting guide** | To objectively determine presence of upper airway oedema during the anaphylactic reaction that contributed to death.  Criteria developed on expert consensus with consideration of upper respiratory descriptors in published grading systems^3, 7, 21, 30^. Laryngeal swelling may occur after multiple laryngoscopy attempts^1^ – first laryngoscopy and autopsy findings have been qualified to take this confounding element into consideration. Number of laryngoscopy attempts is recorded during data extraction. | | |
| **Outcome #** | **Outcome Text Label** | **Outcome Code Set** | **Definition Note** |
| 1 | Yes |  |  |
| 2 | No |  |  |
| 3 | Not recorded |  | Presence **OR** Absence of symptoms **not** recorded |

- 1. **Bronchospasm present**

| **Definition** | Bronchospasm present during anaphylaxis episode | | |
| --- | --- | --- | --- |
| **Data name** |  | **Collection** | Manual extraction |
| **Data Type** |  | **Date Started** | 01/05/2024 |
| **Field Size** | Drop down yes/no/not recorded | **Layout** |  |
| **Code Set** | [bronchospasm] = 1 |  |  |
| **Reporting guide** | Yes if ANY of the following present   - Persistent cough - Wheeze - Chest tightness with history of asthma - Dyspnoea with history of asthma - Cyanosis or hypoxia <93% with history of asthma (excluding isolated upper airway obstruction) - Cyanosis hypoxia <93% without documented or clinical hypotension - Increased work of breathing (excluding isolated upper airway obstruction) - Patient’s usual asthma symptoms - Bronchodilator use during episode - High peak inspiratory pressure in intubated patient (subjective or greater than 30cm H2O) - Difficult to ventilate - Upsloping CO2 trace or obstructive airway pattern | | |

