| **Purpose and basis for reporting guide** | To objectively determine the presence of bronchospasm during the anaphylactic reaction contributing to death.  Criteria developed on expert consensus with consideration of lower respiratory descriptors in published grading systems (^3, 20, 23^3, 6, 7).  Upper airway obstruction, bronchospasm and cardiovascular symptoms can overlap.  Criteria have been developed to exclude overwhelming upper airway obstruction in the absence of obvious bronchospasm. Chest tightness and shortness of breath may be a manifestation of cardiovascular involvement if not associated with asthma symptoms or pre-existing asthma increasing the pre-assessment probability of symptom origin.  Dyspnoea, cyanosis and Hypoxia can overlap with cardiovascular compromise^2, 3^. Brown reported 12 % of hypotensive patients developed *dyspnoea* where 100% of hypoxic patients had either dyspnoea or wheeze. In the same study 10% of wheezy patients had hypotension. | | |
| **Outcome #** | **Outcome Text Label** | **Outcome Code Set** | **Definition Note** |
| 1 | Yes |  |  |
| 2 | No |  |  |
| 3 | Not recorded |  | Presence **OR** Absence of symptoms **not** recorded |

- 1. **Cardiovascular reaction present**

| **Definition** | Cardiovascular reaction present during the anaphylaxis episode | | |
| --- | --- | --- | --- |
| **Data name** | Cardiovascular | **Collection** | Manual extraction |
| **Data Type** | Single answer | **Date Started** | 01/05/2024 |
| **Field Size** | Drop down yes/no/not recorded | **Layout** |  |
| **Code Set** | [cardiovascular] = '1' |  |  |
| **Reporting guide** | Yes if ANY of the following present   - Hypotension without severe respiratory symptoms - Dizziness or feeling faint without severe respiratory symptoms - Dyspnoea without severe respiratory symptoms - Postural dizziness without severe respiratory symptoms - Sweating and nausea without severe respiratory symptoms - Tachycardia meeting red ViCTOR criteria prior to adrenaline and without severe respiratory symptoms - Requiring ongoing vasopressor support even if respiratory symptoms present   Do not say YES if only evidence of cardiovascular reaction is arrest. | | |

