| **Reporting guide** | This is the organ failure type that predominates the reaction – specifically which is most severe.  However if two organ failure elements cannot be delineated between primary and secondary, then the organ with symptoms that were most pronounced first in time should be listed as the primary organ failure type.  A cardiorespiratory arrest that occurs with upper airway oedema or bronchospasm present in isolation should NOT have cardiovascular reaction present after the arrest unless there is prolonged requirement for vasopressor support. | | |
| **Purpose and rationale** | To record the predominant organ failure type leading to cardiorespiratory arrest. | | |
| **Outcome #** | **Outcome Text Label** | **Outcome Text Label** | **Definition Note** |
| 1 | Airway Oedema |  | A cardiorespiratory arrest that occurs predominantly from upper airway oedema symptoms |
| 2 | Bronchospasm |  | A cardiorespiratory arrest that occurs predominantly from bronchospasm symptoms |
| 3 | Cardiovascular |  | A cardiorespiratory arrest that occurs predominantly from cardiovascular symptoms |
| 4 | Pulmonary oedema |  | A cardiorespiratory arrest that occurs predominantly from pulmonary oedema symptoms |
| 5 | Unable to determine |  | Insufficient information to comment. |

- 1. **Secondary Organ Failure Type**

| **Definition** | The organ involvement that was present and contributed less to the cardiorespiratory arrest than the primary organ failure type involved. | | |
| --- | --- | --- | --- |
| **Data name** | secondary_organ_failure | **Collection** | Manual |
| **Data Type** | Dropdown | **Form** |  |
| **Field Size** | 1-5 see below | **Layout** |  |
| **Reporting guide** | This is the organ failure type that was present during the anaphylaxis reaction but was not the primary reason for cardiorespiratory arrest; or was the reaction that occurred second in time if considered equal in magnitude to the primary mechanism.  Example – Upper airway oedema that was observed on laryngoscopy.  in a bronchospasm primary organ failure patient | | |
| **Purpose and rationale** | To record the predominant organ failure type leading to cardiorespiratory arrest. | | |
| **Outcome #** | **Outcome Text Label** | **Outcome Text Label** | **Definition Note** |
| 1 | Airway Oedema |  | A cardiorespiratory arrest that occurs predominantly from upper airway oedema symptoms |

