| radio | Place where severe symptoms/arrest occurred different to where the patient was exposed?  Severe symptoms are:  - SaO2 < 93% or symptoms associated with hypoxia:  - Vomiting, stridor, cyanosis, confusion, dyspnoea and wheeze with increased effort.  OR  - Hypotension or symptoms associated with hypotension  - Vomiting diarrhoea, feeling of impending doom, weakness, dizziness, visual disturbance, diaphoresis, pallor, collapse, incontinence.  OR  - Meets clinical review triggers on ViCTOR charts | 1, Yes \| 2, No \| 3, Not recorded |
| radio | Location where symptoms became severe | 1, Allergy Clinic not part of acute hospital \| 2, Allergy Clinic part of  acute hospital \| 3, Home \| 4, Other friend or family house not home \| 5, School \| 6, Restaurant \| 9, Hospital - Critical Care Area \| 10, Hospital - Other \| 11, Other healthcare (where health practitioner present) \| 12, Radiology - outside hospital \| 13, Radiology - inside hospital \| 14, Ambulance \| 15, Other \| 16, Unknown/Not recorded |
| text | Severe symptom location description |  |
| text | Minutes from exposure to symptoms: |  |
| text | Minutes from first symptoms to severe symptoms |  |
| text | Minutes from severe symptoms to arrest  Arrest occurs when there is  - Sudden bradycardia  - Loss of pulse or BP <50  - Unconscious with ineffective breathing needing assisted ventilation  - Seizure or myoclonic activity (hypoxic/hypotensive)  - Shockable rhythm/asystole |  |
| text | time from arrest to death |  |
| radio | Airway oedema present | 1, Yes \| 2, No \| 3, Not Recorded |
| text | Evidence of upper airway oedema in a few words/sentence |  |
| radio | Bronchospasm present | 1, Yes \| 2, No \| 3, Not Recorded |
| text | Evidence for bronchospasm in a few words/sentence |  |
| radio | Cardiovascular compromise | 1, Yes \| 2, No \| 3, Not recorded |
| text | Evidence for cardiovascular compromise in a few words/sentence |  |
| dropdown | Primary organ failure | 1, Airway \| 2, Bronchospasm \| 3, Cardiovascular \| 4, unable to determine |
| dropdown | Secondary organ failure | 1, Airway \| 2, Bronchospasm \| 3, Cardiovascular \| 4, No secondary organ failure recorded |
| dropdown | Third Organ Failure | 1, Airway \| 2, Bronchospasm \| 3, Cardiovascular \| 4, No third organ failure recorded |

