## Handling of Missing Data

The analyses for all outcomes will be conducted using participants with available data.

However, if there are >10% missing data in the primary or key secondary outcomes (or exposure variables), we will conduct a sensitivity analysis under a plausible assumption regarding the missingness mechanism. Multiple imputation will be used to handle the missing data in all models used for outcomes. Imputations will be generated using chained equations, also known as fully conditional specification, with 50 imputed datasets and 10 iterations between each imputation. Any variables that are predictors of missingness and/or associated with the incomplete outcomes will be included as auxiliary variables in the imputation model. Estimates of interest will be obtained using Rubin’s rules, and will be reported with 95% confidence intervals and *p*-values.

For the analysis of time-to-event outcomes, rather than using multiple imputation, we will handle missing data (i.e. those who did not experience the outcome) by censoring those patients at the time of death.

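### About a third of deaths have no primary organ failure, unevenly by allergen, and no planned analysis can show whether cardiovascular deaths are over-represented among them

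*Combined protocol and SAP*

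**What the plan says.** **Coding rules.** Table 1, cardiovascular reaction field: "Do not say YES if only evidence of cardiovascular reaction is arrest". Table S1 repeats the rule for allocating primary or secondary failure: "Negative/not for inclusion if cardiac arrest only manifestation recorded". The arrest field of Table 1 counts "Loss of pulse or BP <50" as arrest. Upper airway oedema may be coded from post-mortem evidence ("Gross macroscopic laryngeal swelling at autopsy"). Bronchospasm may be coded from findings during resuscitation, such as difficulty ventilating, high inspiratory pressure or bronchodilator use.

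**Unclassifiable deaths.** Table 1 has an unable-to-determine category for primary organ failure, defined as "Insufficient information to comment".

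**Analysis.** SAP, Handling of Missing Data: "The analyses for all outcomes will be conducted using participants with available data". If more than 10% is missing, a sensitivity analysis follows using chained equations, 50 imputed datasets and auxiliary variables, under a missingness assumption called plausible but not named. The sensitivity paragraphs for the primary outcome and in section 6.2 add no other approach to missing outcomes.

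**Code 4.** In Table 1, code 4 for primary organ failure is pulmonary oedema ("A cardiorespiratory arrest that occurs predominantly from pulmonary oedema symptoms"). In Table 2 the same field reads "4, unable to determine" and has no pulmonary oedema option.

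**The concern.** The three mechanisms do not have equal chances of being classified. A sudden collapse with no recorded prodrome cannot be called cardiovascular, and a blood pressure low enough to be the best evidence of cardiovascular failure is itself defined as arrest. Airway and bronchospasm deaths have routes to classification from autopsy or from ventilation during resuscitation. The main late route for a cardiovascular death is a continuing need for vasopressors. Whether the outcome is missing may therefore depend on what the outcome was.

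Available-case analysis ignores such dependence. Chained-equation imputation as normally run fills undetermined deaths from determined deaths with the same recorded covariates, so it carries the same blind spot. Agreement between the two is not reassurance. What is at stake is the reported frequency of each mechanism, which the protocol's Background says is meant to inform treatment recommendations.

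**Working it through.** **Inputs.** Deaths with a known outcome, and mechanism counts, are from Tables S2a and S2b. Total deaths are the vomiting-or-aspiration denominators in Table S4. That item is a checkbox in Table 2 with no not-recorded option, so it can stand for all deaths. In each allergen block of that row, the exposed and unexposed denominators sum to 351.

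**Reproducing a published figure.** Unadjusted complete-case odds ratio, bronchospasm, insect v drug: (9/28)/(68/47) = 0.222. The SE of the log odds ratio is √(1/9 + 1/28 + 1/68 + 1/47) = 0.428, giving 0.096 to 0.514, exactly as in Table S2a. The S2 counts are therefore the analysed denominators.

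**Missing outcome = S4 total − S2 known.**

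| Allergen | Total | Known | Missing | % missing | Bronchospasm | Cardiovascular |
|---|---|---|---|---|---|---|
| Drug | 179 | 115 | 64 | 35.8 | 68 | 40 |
| Insect | 63 | 37 | 26 | 41.3 | 9 | 21 |
| Food | 64 | 58 | 6 | 9.4 | 55 | 0 |
| Contrast | 45 | 27 | 18 | 40.0 | 13 | 12 |
| All | 351 | 237 | 114 | 32.5 | 145 | 73 |

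Chi-square for missingness by allergen is 19.8 on 3 df, p = 0.0002. Without food it is 0.73 on 2 df, p = 0.69, so the imbalance is food against the rest.

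A cross-check: the Table S3 vomiting row covers 53 + 197 = 250 deaths with an allocated mechanism, 13 more than S2. The natural reading is triggers outside the four categories. If all 13 belonged inside them, missing would be 351 − 250 = 101 (28.8%).

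**If missing deaths resemble observed ones within allergen**, the expected cardiovascular count is 64 × 40/115 = 22 for drug and 18 × 12/27 = 8 for contrast, and bronchospasm stays ahead in both.

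**Tipping point.** Let k missing deaths be cardiovascular.

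- Drug, remainder split between bronchospasm and upper airway as observed (68 to 7): 40 + k = 68 + (64 − k) × 68/75, so k = 45.1, or 70% of 64. With the remainder all bronchospasm, 40 + k > 68 + 64 − k first holds at k = 47 (73%).
- Contrast, remainder all bronchospasm: 12 + k > 13 + 18 − k first holds at k = 10 (56%). With the remainder split as observed, it is 9 (50%).
- All deaths, remainder split as observed (145 of 164 non-cardiovascular): 73 + k = 145 + (114 − k) × 145/164, so k = 91.7, or 80% of 114. With the remainder all bronchospasm, 94 (82%).
- Food: 55 bronchospasm against at most 6, so no flip. Insect: cardiovascular already leads 21 to 9.

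The required odds of cardiovascular failure in missing relative to observed deaths (remainder all bronchospasm) are (47/17)/(40/75) = 5.2 for drug and (10/8)/(12/15) = 1.6 for contrast.

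**Bound: every missing death cardiovascular.** Drug: bronchospasm 68/179 = 38.0%, cardiovascular 104/179 = 58.1% (observed 59.1% and 34.8%). All: 145/351 = 41.3% and 187/351 = 53.3%.

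**Unadjusted odds ratios under that bound.**

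- Bronchospasm, insect v drug: (9/54)/(68/111) = 0.27 (0.13 to 0.59); published 0.222.
- Bronchospasm, food v drug: (55/9)/(68/111) = 9.98 (4.63 to 21.47); published 12.672.
- Bronchospasm, contrast v drug: 0.66 (0.33 to 1.35); published 0.642.
- Cardiovascular, insect v drug: (47/16)/(104/75) = 2.12 (1.12 to 4.02); published 2.461.
- Cardiovascular, contrast v drug: 1.44 (0.73 to 2.87); published 1.500.

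This bound moves every allergen the same way. It is not the worst case for a contrast if the departure differs between allergens.

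**The case against.** The strongest reply is that the mechanism is conjecture. No table counts arrest-only deaths or says why any death was undetermined. A poorly documented or unwitnessed bronchospasm death can also be unclassifiable, and the cardiovascular criteria accept low-threshold lay symptoms such as faintness or sweating with nausea. The rule has a rationale: the Background explains that loss of circulation is the final common pathway, including from hypoxia. This stands. A reader might infer that sudden cardiovascular deaths are shown to be the likeliest to be missing; the documents support only that it is plausible.

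A reader might also take the unequal missingness as proof of outcome-dependent missingness. It is not. The difference lies between allergens, and allergen is the exposure in the model, so imputation can condition on it.

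It is tempting to quote a threshold of 55% for drug. That is the share displaced on top of a remainder that itself contains 34.8% cardiovascular deaths. The total share at the flip is 0.548 + 0.452 × 0.348 = 70%.

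The SAP never names missing at random; that is inferred from standard chained equations. The primary question is the between-allergen association, and the unadjusted contrasts above hold up under the bound.

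What does not stand is reliance on complete-case and imputed results being close. Both learn only from determined deaths. Nor are they close for adjusted contrast v drug: upper airway 6.935 (p = 0.001) against 2.565 (p = 0.220), and bronchospasm p = 0.028 against 0.101.

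On code 4, the labels conflict, but nothing shows that any determined pulmonary oedema death was read as missing.

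**Conclusion.** The concern holds in limited form. About a third of deaths in the four categories lack the primary outcome, the fraction is not stated, and the plan has no analysis that could detect enrichment of undetermined deaths for cardiovascular failure. The exposed results are the mechanism frequencies for contrast (flip at about half of the missing), drug (about 70%) and the pooled series (about 80%). A general claim that the plan names the wrong leading mechanism is not supported: food cannot flip, and in insect deaths the suspected bias would only strengthen the existing leader. The unadjusted contrasts recomputed here keep their direction and their position relative to the 5% level; adjusted ones need patient data.

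This rests on the vomiting-row denominators being all deaths (if some are absent, missingness is higher) and on Table S2 holding every classified death in the four categories (if not, it could be as low as 28.8%). It should be fixed, with moderate confidence; it is a cheap improvement and not a fatal flaw.

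**What to change.** 1. Add to the SAP, in Handling of Missing Data and the primary sensitivity analyses, a delta-adjusted multiple imputation that raises the log-odds of cardiovascular failure in undetermined deaths over a stated range, with the shift allowed to differ by allergen. Report the tipping point for each contrast and for the mechanism frequencies. Show all-undetermined-as-cardiovascular as a bound only. State the missingness assumption of the existing imputation.
2. Report undetermined deaths by allergen and reason, including the number that were arrest-only, with all deaths as denominator and subject to the small-cell rule. The free-text evidence field for cardiovascular compromise in Table 2 should allow this count.
3. Reconcile code 4 between Tables 1 and 2, and confirm that no determined pulmonary oedema death was treated as missing.

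The cost is SAP wording, a review of the free-text field and a few more runs on data already held. The downside is that the frequency statements become less definite.

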**1.0 Study Synopsis**

## Primary Objectives

To examine differences in primary organ failure that develop in patients who have fatal anaphylaxis after being exposed to different allergen trigger categories. We define patient allergen exposure to one of four categories of allergens: drug, insect, food, and radiocontrast, where ‘drug’ will be the reference group.

## Secondary Objectives

To compare the following outcomes by patient allergen exposure:

1. Time to symptoms from allergen exposure.
2. Time from symptom onset to severe symptoms.
3. Time from severe symptoms to cardiorespiratory arrest.
4. Time from arrest to death.
5. Whether the patient required tracheal intubation.
   1. If required tracheal intubation, the timing of tracheal intubation.
   2. Time to tracheal intubation from cardiorespiratory arrest.
6. Whether the patient experienced vomiting or aspiration.
7. Whether the patient received cardioversion (defined as no shocks vs at least one shock).
8. Change in posture.
9. Frequency of deaths per year over time (by allergen exposure and by age group).

To compare primary organ failure by the following complications:

1. Difficult airway (FONA, failed intubation, or 3 or more attempts at intubation)
2. FONA (front of neck access)
3. Vomiting or aspiration
4. Pneumothorax (dichotomised to none OR one+/- both sides)
5. Cardioversion

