| text | Time to IV adrenaline after arrest in minutes |  |
| text | Total dose of adrenaline post arrest |  |
| text | Adrenaline notes |  |
| radio | Was a second line vasopressor/cardiovascular support used (includes usuals and glucagon, methylene blue) | 1, Yes \| 2, No \| 3, Not Recorded |
| radio | Noradrenaline | 1, Yes \| 2, No \| 3, Not Recorded |
| radio | Metaraminol | 1, Yes \| 2, No \| 3, Not Recorded |
| radio | Vasopressin | 1, Yes \| 2, No \| 3, Not Recorded |
| radio | Dopamine | 1, Yes \| 2, No \| 3, Not Recorded |
| radio | Dobutamine | 1, Yes \| 2, No \| 3, Not Recorded |
| radio | Glucagon | 1, Yes \| 2, No \| 3, Not Recorded |
| radio | Methylene Blue | 1, Yes \| 2, No \| 3, Not Recorded |
| radio | milrinone | 1, Yes \| 2, No \| 3, Not Recorded |
| text | Notes about second line cardiovascular support |  |
| Yes/no | Other resuscitation? Did the patient receive resuscitation eg fluids, oxygen, bronchodilators, DCR from any healthcare staff |  |
| radio | Crystalloid use before arrest | 1, Yes \| 2, No \| 3, Not recorded |
| radio | Crystalloid use after arrest | 1, Yes \| 2, No \| 3, Not recorded |
| radio | Salbutamol use | 1, Yes \| 2, No \| 3, Not recorded |
| radio | Ipratropium Use | 1, Yes \| 2, No \| 3, Not recorded |
| radio | Steroid Use | 1, Yes \| 2, No \| 3, Not recorded |
| radio | NIV Use | 1, Yes \| 2, No \| 3, Not recorded |
| radio | Bag and Mask Ventilation only | 1, Yes \| 2, No \| 3, Not recorded |
| radio | FONA front of neck access | 1, Yes \| 2, No \| 3, Not recorded |
| radio | ECMO VV | 1, Yes \| 2, No \| 3, Not recorded |
| radio | ECMO VA | 1, Yes \| 2, No \| 3, Not recorded |
| radio | Intubated | 1, Yes \| 2, No \| 3, Not recorded |
| radio | 1 or 2 shocks required at any time | 1, Yes \| 2, No \| 3, Not recorded |
| radio | 3 or more shocks required at any time | 1, Yes \| 2, No \| 3, Not recorded |
| text | Time from arrest to ECMO in minutes |  |
| dropdown | When was the patient intubated | 1, Intubated before reaction \| 2, Intubated before arrest \| 3, Intubated after arrest |
| dropdown | How many attempts at intubation? | 1, 1 \| 2, 2 \| 3, 3 \| 4, 4 \| 5, 5 \| 6, More than 5 |
| checkbox | Who intubated/attempted to intubate the patient | 1, Paramedic \| 2, ED Physician \| 3, Anaesthetist \| 4, Intensivist \| 5, GP Anaesthetist/generalist |
| text | Minutes to successful definitive intubation from arrest |  |
| text | Free text notes about intubation |  |

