**Association of complications with primary outcome and allergen trigger category**

As a condition of ethics approval, death counts of less than five cannot be directly reported. Where this has occurred in tabular reporting, we have abbreviated this to Not Reportable (NR).

**Table S3:** Association between complication and primary organ failure

|  | **Number (%) with specified primary organ failure** | **Number (%) without specified primary organ failure** | **Complete case analysis** | | **Multiple imputation** | |
| --- | --- | --- | --- | --- | --- | --- |
|  |  |  | **Odds ratio (95% CI)** | **p-value** | **Odds ratio (95% CI)** | **p-value** |
| **Primary Organ Failure: Bronchospasm** | | | | | | |
| **Difficult airway** | 21/29 (72.4%) | 101/160 (63.1%) | 1.533 (0.639 to 3.680) | 0.338 | 1.523 (0.668 to 3.473) | 0.316 |
| **Cricothyroidotomy** | 5/13 (38.5%) | 122/193 (63.2%) | 0.364 (0.115 to 1.155) | 0.086 | 0.380 (0.130 to 1.117) | 0.078 |
| **Vomiting or aspiration** | 37/53 (69.8%) | 116/197 (58.9%) | 1.615 (0.842 to 3.098) | 0.149 | 1.774 (0.944 to 3.334) | 0.075 |
| **Pneumothorax** | 11/18 (61.1%) | 129/209 (61.7%) | 0.975 (0.363 to 2.617) | 0.959 | 1.014 (0.363 to 2.835) | 0.979 |
| **Cardioversion** | 26/41 (63.4%) | 32/46 (69.6%) | 0.758 (0.310 to 1.853) | 0.544 | N/A | N/A |
| **Primary Organ Failure: Cardiovascular** | | | | | | |
| **Difficult airway** | NR | 53/160 (33.1%) | 0.150 (0.034 to 0.653) | 0.011 | 0.206 (0.053 to 0.807) | 0.024 |
| **Cricothyroidotomy** | NR | 55/193 (28.5%) | 0.753 (0.200 to 2.839) | 0.675 | 0.974 (0.273 to 3.475) | 0.967 |
| **Vomiting or aspiration** | 12/53 (22.6%) | 61/197 (31.0%) | 0.653 (0.321 to 1.328) | 0.239 | 0.618 (0.313 to 1.220) | 0.165 |
| **Pneumothorax** | 5/18 (27.8%) | 60/209 (28.7%) | 0.955 (0.326 to 2.796) | 0.933 | 0.992 (0.344 to 2.858) | 0.988 |
| **Cardioversion** | 12/41 (29.3%) | 12/46 (26.1%) | 1.172 (0.457 to 3.005) | 0.740 | N/A | N/A |
| **Primary Organ Failure: Upper airway** | | | | | | |
| **Difficult airway** | 6/29 (20.7%) | 6/160 (3.8%) | 6.696 (1.990 to 22.531) | 0.002 | 3.401 (1.126 to 10.269) | 0.030 |
| **Cricothyroidotomy** | 5/13 (38.5%) | 16/193 (8.3%) | 6.914 (2.023 to 23.629) | 0.002 | 5.530 (1.627 to 18.804) | 0.006 |
| **Vomiting or aspiration** | NR | 20/197 (10.2%) | 0.722 (0.236 to 2.212) | 0.569 | 0.653 (0.216 to 1.971) | 0.449 |
| **Pneumothorax** | NR | 20/209 (9.6%) | 1.181 (0.253 to 5.513) | 0.832 | 1.133 (0.206 to 6.232) | 0.886 |

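### Table S3 implies fewer cardiovascular deaths with a difficult airway than with front of neck access, although under the SAP definition front of neck access alone makes an airway difficult

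*Combined protocol and SAP*

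**What the plan says.** The SAP's Secondary Objectives list five complications to be compared with primary organ failure. The first is "Difficult airway (FONA, failed intubation, or 3 or more attempts at intubation". The second is one of its components taken alone, "FONA (front of neck access". SAP section 6.1 repeats both items and makes these comparisons unadjusted and descriptive. Under Handling of Missing Data, analyses use participants with available data, with multiple imputation as a sensitivity analysis.

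Table S3 reports primary organ failure within each complication group. Its difficult-airway rows read:

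- bronchospasm: "21/29 (72.4%) | 101/160 (63.1%) | 1.533 (0.639 to 3.680"
- cardiovascular: "NR | 53/160 (33.1%) | 0.150 (0.034 to 0.653"
- upper airway: "6/29 (20.7%) | 6/160 (3.8%) | 6.696 (1.990 to 22.531"

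FONA appears in the table under the label Cricothyroidotomy. Its cardiovascular count is also suppressed, and the odds ratio is "0.753 (0.200 to 2.839". NR marks counts below five, which the ethics approval does not allow to be reported directly.

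On the data side, Table 2 of the protocol has a Yes/No/Not recorded field for FONA and a dropdown, "How many attempts at intubation", whose options run from 1 to more than 5.

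**The concern.** A composite that is positive when any component is positive cannot have fewer positives than one of its components, in the whole cohort or in any stratum. Blanks in the other components do not alter this, because a recorded FONA settles the composite. If a stratum of Table S3 breaks the rule, the variable analysed is not the one the SAP defines, and all three difficult-airway rows are affected because they share the same positives and negatives.

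These rows matter to a reader of the table. Difficult airway supplies two of its nominally significant complete-case results: cardiovascular (p=0.011) and upper airway (p=0.002). The SAP asks for interpretation by the size of the estimates and their intervals, so an error in size counts even where the p-value stays below 0.05.

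**Working it through.** **Inputs.** All come from Table S3, complete-case columns. Write *a* for the suppressed cardiovascular count with a difficult airway and *f* for the suppressed cardiovascular count with cricothyroidotomy. The two cells are left as expressions here because of the suppression rule.

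**Step 1: the rows close.** Without the complication, the three organ-failure types account for everyone: 101 + 53 + 6 = 160 for difficult airway, and 122 + 55 + 16 = 193 for cricothyroidotomy. The suppressed cells therefore follow by subtraction:

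- *a* = 29 − 21 − 6
- *f* = 13 − 5 − 5
- *f* − *a* = (13 − 10) − (29 − 27) = 1

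**Step 2: reproduce the printed odds ratios.** For a 2×2 table, OR = (x/(n₁ − x)) / (y/(n₀ − y)), with 95% CI exp[ln OR ± 1.96 √(sum of reciprocals of the four cells)].

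- Difficult airway: (*a*/27) / (53/107) = 0.150 (0.034 to 0.653), p=0.011. This matches the print. One more case among the 29 would give 0.233 and one fewer 0.072.
- Cricothyroidotomy: (*f*/10) / (55/138) = 0.753 (0.200 to 2.839), p=0.675. This also matches. One fewer case among the 13 would give 0.456 and one more 1.115.
- The four unsuppressed rows reproduce too: bronchospasm 1.533 and 0.364, upper airway 6.696 and 6.914.

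Subtraction and the odds ratios agree, so the difficult-airway count is one below the FONA count. At least one FONA-positive cardiovascular death is not counted as a difficult airway.

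**Step 3: denominators.** Known values number 29 + 160 = 189 for difficult airway and 13 + 193 = 206 for cricothyroidotomy, a gap of 17. By organ failure:

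- upper airway: (5 + 16) − (6 + 6) = 21 − 12 = 9
- bronchospasm: (5 + 122) − (21 + 101) = 127 − 122 = 5
- cardiovascular: (*f* − *a*) + (55 − 53) = 3

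**Step 4: correct the one proven record.**

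| Row | Printed | Record had been missing | Record had been coded No |
|---|---|---|---|
| Cardiovascular | 0.150 (0.034 to 0.653), p=0.011 | ((*a*+1)/27)/(53/107) = 0.224 (0.065 to 0.773), p=0.018 | ((*a*+1)/27)/(52/107) = 0.229 (0.066 to 0.788), p=0.019 |
| Upper airway | 6.696 (1.990 to 22.531) | (6/24)/(6/154) = 6.417 (1.912 to 21.531) | (6/24)/(6/153) = 6.375 (1.900 to 21.392) |
| Bronchospasm | 1.533 (0.639 to 3.680) | (21/9)/(101/59) = 1.363 (0.586 to 3.171) | (21/9)/(101/58) = 1.340 (0.576 to 3.119) |

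**Step 5: must more records be lost?** No. Take the deaths with a known composite as a subset of those with known FONA.

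- Upper airway: all 5 FONA positives can lie among the 6 difficult-airway positives. The 16 FONA negatives then split into 1 positive, 6 negative and 9 missing.
- Bronchospasm: all 5 FONA positives can lie among the 21. The 122 FONA negatives then split into 16 positive, 101 negative and 5 missing.

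Both fit with no further FONA positive lost.

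**The case against.** **Different labels.** Table S3 says cricothyroidotomy where the SAP says FONA. The row takes FONA's place in the SAP list. If cricothyroidotomy is only one form of FONA, the true FONA count is at least as large and the contradiction stands or grows.

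**Different denominators.** Available-case analysis can legitimately use 189 deaths in one row and 206 in another. It cannot remove a death with FONA recorded, because that death's composite value is known. No section restricts the composite to a subset such as intubated patients.

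**Imputation covers it.** The imputed cardiovascular odds ratio, 0.206 (0.053 to 0.807), is close to the corrected complete-case value. That is no repair: a record set to missing would have a known Yes treated as unknown, and a record coded No would not be imputed at all.

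**Little is at stake.** This has force. The analyses are descriptive and unadjusted, the proven error is one record, and no conclusion is shown to reverse. The SAP definition itself is sound; the discrepancy lies in the results table.

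A reader might also go further than the documents allow:

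- *Several known positives were dropped, mainly among upper-airway deaths.* The gap of 21 against 12 counts deaths without a composite value, not lost positives. If FONA is No and the number of attempts is unrecorded, a missing composite is legitimate. Step 5 shows that no upper-airway positive need have been lost.
- *The cardiovascular result loses significance.* An odds ratio of 0.374 (0.136 to 1.026), p=0.056, requires every cardiovascular FONA death to have been left out as missing and no other FONA death. Nothing shows this.
- *Table S4 is wrong too.* Its recoverable difficult-airway counts are never below its FONA counts: for example drug 14 against 5 and insect 5 against 5.

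**Conclusion.** The contradiction is arithmetically certain, given that the cricothyroidotomy row holds FONA cases and that the SAP definition is the one meant to apply. One uncounted cardiovascular record is proven. The printed difficult-airway odds ratios in Table S3 are therefore not those of the defined variable.

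The minimum correction raises the cardiovascular odds ratio by about half (0.224/0.150 ≈ 1.5), while the upper-airway estimate barely moves. Both keep their direction and nominal significance. If further FONA positives were also left out as missing (1 to 3 cardiovascular, 0 to 5 in each other type), the cardiovascular odds ratio would lie between 0.164 and 0.374. That range is a bound, not a finding. The mechanism remains open: the fall from 206 to 189 known values fits a missing composite, but coding as No is equally consistent with the counts.

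**What to change.** 1. Derive difficult airway as Yes whenever any component is Yes, whatever is blank elsewhere.
2. Treat never-intubated patients without FONA as structural negatives, or exclude them explicitly. The attempts field has no zero, not-applicable or not-recorded option, so a rule that demands a known negative on every component would wrongly set these patients to missing.
3. State how failed intubation is obtained, since Table 2 of the protocol has no separate field for it.
4. Rerun the difficult-airway rows of Table S3, complete case and imputed, deriving the composite from its components within the imputation. Check the corresponding rows of Table S4.
5. State the denominator used, and add a programmed check that composite positives are never fewer than FONA positives in any stratum.
6. Keep to the small-count suppression rule in any correction.

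If a different definition was in fact used, the alternative is to state it together with its denominator.

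The cost is a short recode, a rerun and replacement of a few table rows. FONA and attempts are already collected. Failed intubation may need a reading of the intubation notes already extracted.
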